### VR setup and experimental manipulation

To modify smoking-related approach biases, we apply a novel VR setup, which is based on the AAT-training previously used by our research group [12]. Participants perform trainings in a standing position and are equipped with HTC Vive HMD, which has a resolution of 2160 × 1200 pixels and a refresh rate of 90 Hz (HTC Corporation, ViveTM). The Leap Motion infrared sensor (Leap Motion, Inc., San Francisco, CA) is used to transfer the participants’ own hand movements into the VR, thereby enhancing body ownership and immersion. The training was implemented using the Unity3D engine; therefore, the C# language was used for programming the scripts. Smoking and control items were obtained from the Unity3D asset store and were modified in terms of color and size.

The VR scenario places participants inside a virtual office space in which they are instructed to interact with virtual smoking-related objects and nonsmoking control objects using their dominant hand (*see* Fig. 2). Each training begins with the participant making a thumbs-up gesture. During the trial, 10 different smoking (i.e., cigarette, cigar, cigarette lighter, cigarette pack, or ashtray) and 10 shape- and color-matched control objects (pen, toothbrush, mug, drinking bottle, book, tennis ball, apple, or avocado) appear consecutively in the middle of a virtual desk. The items are bordered in either red or blue. Participants are asked to ignore item content and to respond to border color by using their own hand.

**Fig. 2 Fig2:**
[figure not shown]
Virtual reality setting. (A) VR environment. The upper line of the Fig. 1 shows the VR-AAT avoidance condition, the bottom line (2) shows the VR-AAT placebo condition. (B) Thumb-up gesture to start the training. (C) Participants’ view of a smoking-related item (here: cigarette). (D) Participant equipped with the HTC Vive head-mounted display and interacting with a smoking-related VR item: (1) pushing a cigarette in the VR-AAT avoidance condition vs. (2) sorting a cigarette to the right in the VR-AAT placebo condition. (E) Participant interacting with a smoking-unrelated VR item: (1) grasping a toothbrush in the VR-avoidance condition vs. (2) sorting a toothbrush to the left in the VR-placebo condition.

In the VR-avoidance training, smokers are instructed to respond to red-bordered objects by making a warding arm movement and throwing them as quickly as possible into a trashcan placed behind the desk. In addition, they should respond to blue-bordered objects by making a grasping movement and placing them as quickly as possible into a box in front of the desk. Importantly, all smoking-related objects are bordered in red and must be avoided, whereas all smoking-unrelated objects are bordered in blue and must be grasped. Thus, consistent with other CBM studies, an indirect instruction was employed.

The VR-placebo training is similar to the VR-avoidance training in that it requires participants to ignore item content and to react to border color. However, this task abstains from using any approach (i.e., grasping) or avoidance (i.e., warding) movements. That is, participants are asked to respond as quickly as possible to the objects appearing on the desk by placing blue-bordered objects into a box positioned on the left-hand side of the desk and red-bordered objects into a box on the right-hand side of the desk. In addition, no contingency between item content and box position existed.

To ensure training fidelity, a cover story is used in both conditions in which participants receive a credible explanation for the training being arranged as it is. That is, participants in the VR-avoidance training will be told that the training constitutes an avoidance training, while participants in the VR-placebo training are told that the training constitutes a cognitive control training. To ensure that both cover stories are plausible to the participants, we will apply a training evaluation questionnaire of the VR training program in the post-test and follow-up assessments.

Participants must execute the correct movement to make the item disappear. Each item is shown six times, resulting in 120 trials per training. Training sessions take approximately 15 min to complete.

### Material and measures

#### Cognitive bias assessment

The approach, attentional, and association biases for smoking will be measured at pretest, post-test, and follow-up to investigate whether the VR-training is capable of changing existing cognitive biases associated with smoking.

#### Approach bias assessment

Automatic approach biases for smoking-related stimuli will be measured by means of both the standard version of the joystick-AAT (see [8]) and the VR-based AAT. During the standard AAT, 25 smoking-related and 25 positive images derived from Baird et al. [13] appear on a computer screen. Images are tilted 3° to the left or 3° to the right. A joystick (Logitech Extreme 3D) is connected to the computer, and participants are told to use the joystick to push images rotated to the right and to pull images rotated to the left. As a result, images shrink or grow in size depending on the arm movement. For the purpose of bias assessment, smoking and control pictures have to be pulled and pushed equally often. Each picture is shown once in push-away format und once in pull-closer format, resulting in 100 assessment trials. Approach biases derived from the standard AAT are computed for each of the laboratory sessions (pretest, post-test, 7-week follow-up).

The assessment version of the VR-AAT is similar to the VR-avoidance training, with the exception that the 10 smoking-related and 10 smoking-unrelated objects must be grasped and warded off equally often, thereby enabling bias assessment. Each item appears three times in a grasping format and three times in a warding off format, resulting in 120 assessment trials.

An approach bias is inferred from faster pulling/grasping than pushing/warding an item. That is, an approach bias score is calculated by subtracting median reaction times (RT) for pulling an item from median RTs for pushing the exact same item. The reaction time is defined as the time in milliseconds required by a participant to execute the correct full arm movement. Accordingly, a positive value indicates an approach tendency toward a picture category, whereas a negative value indicates an avoidance tendency.

#### Attentional bias assessment

Automatic attention biases for smoking cues will be measured by a visual dot probe task adapted from Miller and Fillmore [22]. The task will be operated using Inquisit Lab software and will be performed on a personal computer. Each trial starts with a 500-ms fixation cross in the center of the computer screen. Afterwards, two 13 × 18 cm images (a smoking-related and a control picture) appear side-by-side and 3 cm apart on the left and right side of the computer screen. Image position is randomly chosen to be either left or right of the location of the fixation cross. After 1000 ms, the two pictures disappear, and a probe stimulus (here: “X”) appears in the location of one of the pictures. A response pad (Cedrus Response Pad RB844) is attached to the computer, and participants are instructed to press a yellow key if the probe is left and to press a green key if the probe is right.

The task stimulus consists of 10 smoking-related images that were matched with 10 neutral tooth-cleaning control images. This image set was provided by Stippekohl and colleagues [23] and has been previously used in recent studies conducted by members of our research group [8, 12, 24]. This pictures bring the advantage of being carefully matched in terms of colors and shape (see [23]). In addition, all images contain a simple smoking or tooth-cleaning behavior without any distractors. This is crucial since evidence hints to the fact that complex addiction-related scenes might be less effective at capturing participants’ attention and could therefore result in less attentional bias when used in visual probe tasks [22]. Each image pair is presented four times, resulting in 40 test trials. In addition, 40 filler trials are included that consisted of 10 pairs of neutral images. This approach is used to reduce possible habituation to smoking-related stimuli that might occur otherwise [25]. Test and filler trials are presented randomly, resulting in 80 trials in total. Filler trials are not included in the final data analysis.

An attentional bias is inferred from faster reaction times to probes that replace a smoking-related image relative to those that replace a tooth-cleaning control image. For the calculation of an attention bias score, RTs for probes replacing the smoking pictures were subtracted from RTs for probes replacing the tooth-cleaning pictures. Thus, a positive value indicates an attention bias toward smoking-related pictures, whereas a negative value indicates an attention bias in favor of tooth-cleaning pictures.

#### Association bias assessment

Implicit positive or negative associations for smoking will be assessed by an implicit association task (IAT [26];). The task is adapted from Kahler and colleagues [27]. Participants are instructed to categorize positive and negative attributes (e.g., “trustful” vs. “hurtful”) and target items (e.g., images of smoking-related objects or furniture, i.e., a cigarette vs. a chair) into predetermined categories via response pad button presses (Cedrus Response Pad RB844).

Following Greenwald et al. [28], the IAT is organized into seven blocks: (a) a 24-trial target discrimination block (e.g., press yellow for “smoking” vs. press green for “furniture”); (b) a 24-trial attribute discrimination block (e.g., yellow for “I feel positive” vs. green for “I feel negative”); (c) a 24-trial practice combined block (e.g., yellow for “smoking” OR “I feel positive” vs. green for “furniture” OR “I feel negative”); (d) a 40-trial test combined block (same as practice); (e) a 24-trial target discrimination block, in which the target categories are reversed (e.g., yellow for “furniture” vs. green for “smoking”); (f) a 24-practice combined block with reversed target categories (e.g., yellow for “furniture” OR “I feel positive” vs. green for “smoking” OR “I feel negative”), and (g) a 40-trial test combined block (same as practice). Blocks c, d, f, and g are crucial blocks used in scoring the IAT.

Because we assume that smokers associate smoking with positive feelings, trials in which smoking and positive consequences share a response key are congruent, whereas trials in which smoking and negative consequences share a response key are incongruent.

The IAT is counterbalanced in two ways to prevent methodological confounds. First, the placements of the target and attribute stimuli labels are counterbalanced (yellow or green button). Second, two IAT orders are used: one with the congruent combination block first and one with the incongruent combination block first.

The IAT bias score is calculated by subtracting RTs for incongruent blocks (i.e., smoking + negative; furniture + positive) from RTs for congruent blocks (i.e., smoking + positive; furniture + negative). Larger IAT scores suggest stronger, implicit, positive, social associations with smoking or stronger, implicit, negative associations with furniture.

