Most recently, the Approach-Avoidance Task (AAT)—originally designed to assess automatic avoidance tendencies in spider-anxious individuals [10]—has proven useful in both measuring and modifying approach biases for appetitive behaviors, including smoking [8, 9]. During the task, various images appear on a computer screen. Participants are instructed to ignore image content and to respond to a content-irrelevant feature such as image format or orientation by either pulling or pushing a joystick attached to the computer. Upon a pull movement, the picture increases in size, whereas upon a push movement, the picture shrinks. This zooming feature disambiguates the task and creates a visual sense of approach and avoidance. An approach bias is inferred from faster pulling than pushing of a picture of interest. Hence, the AAT can be viewed as a measure of performance deficits due to the incongruence between the instructed movement and the automatically triggered response. Using the AAT, an approach bias for cigarette cues was found in smokers but not in ex-smokers or those who have never smoked [9]. A study conducted by Watson and colleagues [11] showed that acute exposure to nicotine (i.e., smoking a cigarette) led to an increased nicotine-related approach bias. Finally, a study by our own working group [8] showed that smokers display an automatic approach bias for smoking cues but not for natural rewards (such as highly palatable food).

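### The printed IAT formula and its stated interpretation run in opposite directions, so a training effect on association bias could be reported backwards (secondary outcome, direction only)

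*Protocol article*

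**What the plan says.** All of the conflicting text is in the protocol article, Association bias assessment.

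- Labels: "trials in which smoking and positive consequences share a response key are congruent". Pairing smoking with the negative side on one key is labelled incongruent. The reason given is that smokers are assumed to link smoking with positive feelings.
- Formula: the score is obtained by "subtracting RTs for incongruent blocks (i.e., smoking + negative; furniture + positive) from RTs for congruent blocks".
- Reading: "Larger IAT scores suggest stronger, implicit, positive, social associations with smoking or stronger, implicit, negative associations with furniture".

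Outcome measures lists the IAT among the secondary outcomes. Data preparation and planned analyses gives the association bias its own 2 (condition) × 3 (time) mixed ANOVA. Neither section redefines the score or its direction.

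**The concern.** To subtract A from B is to form B minus A, so the printed score is the congruent reaction time minus the incongruent one. Congruent blocks are those expected to be easy for someone who likes smoking. The stronger the liking, the shorter the congruent time relative to the incongruent time, and the smaller the printed score. The next sentence tells the reader the opposite.

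The question for this outcome is whether training changes the association, and in which direction. If the analyst computes the score as printed and the author interprets it as printed, a weakening of positive smoking associations in the avoidance group appears as an increase in the score and is described as a strengthening. A benefit would be written up as a harm, and a harm as a benefit.

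**Working it through.** The protocol gives no numerical IAT value to reproduce, so the check is one of sign.

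**Inputs from the document**

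- C = reaction time in congruent blocks (smoking + positive, furniture + negative).
- I = reaction time in incongruent blocks (smoking + negative, furniture + positive).
- Printed score: S = C − I.
- Stated reading: larger S means a stronger positive association with smoking, or a stronger negative one with furniture.
- Reaction-time logic: a mismatch with the automatic tendency slows the response. Background describes the approach-avoidance task (AAT) in these terms, as "a measure of performance deficits due to the incongruence between the instructed movement and the automatically triggered response", and the approach and attentional scores both infer bias from faster responses.

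**Direction**

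Let a = I − C, the advantage of congruent over incongruent blocks. A stronger positive association with smoking makes a larger. So does a stronger negative association with furniture, because that pairing also sits in the congruent blocks. Since S = C − I = −a, the printed score falls as either association strengthens. Both halves of the stated reading are therefore reversed.

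**Numbers** (I = 800 ms is assumed for illustration; the document gives no reaction times)

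| a (ms) | C (ms) | I (ms) | Printed, C − I | Reversed, I − C |
|---|---|---|---|---|
| −100 | 900 | 800 | +100 | −100 |
| 0 | 800 | 800 | 0 | 0 |
| +100 | 700 | 800 | −100 | +100 |
| +200 | 600 | 800 | −200 | +200 |

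Suppose training halves the advantage from 200 to 100 ms. The printed score moves from −200 to −100, a rise of 100 ms, which the stated reading calls a stronger positive association. The reversed score moves from +200 to +100, a fall of 100 ms, which the same reading correctly calls a weaker one. The choice of 800 ms does not matter, because S = −a for any reaction times.

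**Comparison with the other two scores**

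- Approach bias (Approach bias assessment): pull times are subtracted from push times, giving push − pull, and positive means approach.
- Attentional bias (Attentional bias assessment): "RTs for probes replacing the smoking pictures were subtracted from RTs for probes replacing the tooth-cleaning pictures", giving control − smoking, and positive means a bias toward smoking.

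In both, the time for the bias-consistent response is the one taken away, so a larger score means more bias. In the IAT formula it is the one taken from. The document thus uses the same phrasing correctly twice, which rules out an unusual use of the phrase as the explanation.

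**Effect on the test**

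Replacing S by −S changes the sign of every mean and contrast. Sums of squares, and hence F and p, stay the same. A simulated comparison of two groups of 50 confirmed this: t = −2.18 with one sign and +2.18 with the other, p = 0.031 both times.

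**The case against.** The best case on the other side accepts the contradiction and disputes its weight. Most of it stands.

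- The IAT is a secondary outcome, and a sign change alters no F, p or effect magnitude. A reader might infer that error rates, power or the primary results are compromised. They are not: the primary outcomes are approach bias, nicotine consumption and abstinence, and none uses this score.
- No scoring code is shown. A reader might infer that the scoring itself is wrong, but the slip may be only in the prose. The labels are coherent and the two sibling scores are correctly signed, which fits two terms swapped in one sentence. The document supports a check of the code, not a presumption of error in it.
- A reader might expect correlations between the IAT and the other bias scores to be reversed too. No such correlation is planned. The discriminant analyses follow the MANOVA on CO, FTND, smoking attitude and motivation to quit, which does not include the IAT.
- A reader might say that a negative score would be taken to show a negative view of smoking. The section gives no meaning to negative values or to zero; it says only what larger scores suggest. The ordering is what is reversed.
- The text proves an inconsistency and does not prove which sentence is at fault. Reversing the interpretation would restore consistency equally well.

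None of this removes the conflict. The article fixes this scoring rule explicitly, so it cannot be treated as a detail left to an analysis plan. No transformation is stated that would turn the scale round.

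**Conclusion.** The point holds as an internal contradiction that is wrong as written. With the document's own labels, the printed formula and the printed reading cannot both be right. If both are followed, the direction of any training effect on association bias is reported in reverse. The size is a complete reversal of direction on one secondary outcome, with no change in statistical significance or effect magnitude.

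The conclusion rests on one assumption, which the protocol itself makes for its other tasks: responses that agree with an automatic tendency are faster. It does not depend on the illustrative reaction times. Whether a reported result would in fact be reversed depends on the score being both computed and interpreted as printed, which the document cannot settle.

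**What to change.** Reconcile the two sentences. The preferable way is to define the IAT score as the reaction time in incongruent blocks minus that in congruent blocks. This keeps the stated interpretation and makes a larger score mean more bias, as it does for the AAT and dot-probe scores. The alternative is to keep the formula and reverse the interpretation. That is statistically equivalent but leaves the IAT running against the other two measures.

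Then verify that the scoring code uses the chosen direction before the association-bias ANOVA is interpreted, and state that direction wherever the result is reported. The cost is one sentence and one check of the code, changed only if it does not already match. No data collection, sample size or test is affected.

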### Biochemical verification

Expired carbon monoxide (CO) will be assessed at baseline, post-training, and 7-week follow-up using a Carbon Monoxide Monitor (piCO™ Smokerlyzer®; Bedfont Scientific Ltd).

### Behavioral and self-report measures

To track daily nicotine consumption, participants are asked to self-monitor their smoking behavior via a cigarette-tracking app, which was specifically designed for the purpose of this study. To do so, participants log each smoked cigarette directly after smoking. In addition, participants will be asked to estimate their average daily nicotine consumption at pretest, following each training session, post-test, and 7-week follow-up.

The questionnaire measures will include the Fagerström Test for Nicotine Dependence (FTND) [29] (German version: [30]); the Stages of Change Scale [31] (German version: [32]); the Thoughts About Abstinence Scale [33]; attitudes toward smoking based on Swanson et al. [34]; cigarette craving on a 6-point Likert-scale, ranging from 0 (“not at all”) to 5 (“very high”); and the Barratt Impulsiveness Scale (BIS) [35]. Finally, participants provide information about various health-related behaviors, including eating habits, sports activities, and attending medical check-ups. At post-test, participants will be also required to evaluate the VR-training and indicate their awareness about training contingency.

### Outcome measures

Primary outcome measures are changes in approach bias, which are measured by the assessment versions of the joystick-AAT and the VR-AAT, reductions in nicotine consumption, and abstinence rates. Secondary outcome measures will be changes in other cognitive biases as measured by a visual dot-probe task and the IAT, motivation to stop smoking, other health-related behavior, expired CO, cigarette craving, and explicit attitudes toward smoking.

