Although the exact training mechanisms remain uncertain, cognitive bias trainings apparently must be administered multiple times to generalize to real-world behavior and to produce reliable and stable changes over time. This requires participants to be willing to maintain adherence to a daily or weekly training prescription. However, adherence to the trainings might be limited, as trainings are often perceived as monotonous or boring. Confirming the above-mentioned concerns, preliminary evidence suggests that high dropout rates can be challenging for CBM studies [12, 15, 16]. Another reason for rather small training effects concerns the generalization of training to actual everyday behavior. It has been argued that the interaction with simple two-dimensional images reduces the realism of the training and thereby narrows the ecological validity of the task [17]. Virtual reality (VR) simulates a natural environment by presenting an interactive three-dimensional space that mirrors everyday-like arm or posture movements [18]. The realism and immersion created by VR can reasonably be assumed as possibly contributing to the ecological validity and enhancing the engagement, enjoyment, and—most importantly—training adherence [19]. Therefore, this study introduces a novel VR approach bias training (VR-AAT) for smoking as an add-on to brief behavioral counseling for smoking cessation. Our objective is to investigate whether the newly developed VR-AAT is capable of modifying existing approach biases for smoking cues and/or changing smoking behavior by promoting abstinence or reduction of nicotine consumption. The study utilizes a randomized placebo-control design and multi-session VR training during a 2-week training period. We expect that the VR-AAT would reduce smoking-related approach biases as measured with the assessment version of the AAT [8], reduce the number of daily smoked cigarettes, and increase abstinence rates over and above the placebo-control condition.

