## Methods/Design

### Trial design

The present study is a randomized control trial comparing self-report, behavioral, and biochemical outcomes of the VR-AAT training to an active placebo control condition (Additional file 1). Smokers are randomly assigned either to the experimental (brief smoking cessation intervention, hereafter referred to TAU + VR-avoidance training) or to the sham-control condition (TAU + VR-placebo training). This study employs a 2 (condition: avoidance training vs. placebo training) × 3 (time: pretest/post-test: 3 weeks after baseline/follow-up: 7 weeks after baseline) mixed design. Because we expect the experimental condition to be more effective than the sham-training control condition, this protocol describes a superiority trial design. The training intervention occurs over the course of 2 weeks in which smokers complete six training sessions in total. Measures of cognitive biases (approach, attention, and association bias), self-report measures of smoking behavior and biochemically verified smoking intensity are applied at the pretest, post-intervention, and 7-week follow-up.

A priori power analyses were conducted using G*Power 3.1 (open-source software) [20]. Previous research on the efficacy of CBM trainings found a small to moderate effect size [12, 21]. We conducted a power analysis for a 2 × 3 mixed design ANOVA to detect a small-to-moderate effect (Cohen’s d = .30). Our results indicated that a total sample size of 74 is required to achieve 80% power at an alpha level of 0.05 and an assumed correlation of r = .50 between the repeated measures. Because we expect some attrition due to our multisession design, we decided to include 100 participants, which is 50 per condition.

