### Data preparation and planned analyses

So that missing data can be filled in, multiple imputation and the modified Intention-To-Treat (ITT) principles [36] will be used. Prior to computation of the cognitive bias scores, error trials will be excluded from further analyses. Median reaction times will be used to minimize the influence of outliers.

To test for changes in cognitive biases, mixed design ANOVAs will be calculated. Due to random assignment to the experimental or to the placebo group, we expect a priori group differences to be small. Possible chance baseline imbalance between treatment arms will be taken into account by means of follow-up simple effects analyses. For approach biases, a 2 (condition: VR-avoidance training vs. VR-placebo training) × 2 (item content: smoking vs. control items) × 3 (time: pretest, post-test, follow-up) mixed design ANOVA will be conducted. For attentional and association biases, two separate 2 (condition) × 3 (time) mixed design ANOVAs will be calculated.

To evaluate the effects of training on self-reported average daily nicotine consumption, a 2 × 3 mixed ANOVA will be carried out in which the training condition is a between-subjects factor and time (pretest, post-test, follow-up) is a within-subjects factor.

Multilevel modeling (MLM) will be used to estimate the growth curve for nicotine consumption as measured with the cigarette-training app and craving ratings over time.

To explore whether the VR-training leads to increased abstinence rates, a Chi-square test will be computed.

To test the effect of training on other smoking-related variables (i.e., CO, FTND, smoking attitude, motivation to quit), a 2 (condition) × 3 (time) repeated measures MANOVA will be conducted. Significant multivariate effects will be followed up with separate ANOVAS on each dependent variable. In case of significant interactions, discriminant factor analyses will be conducted to identify possible associations between each of the dependent variables and group assignment.

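### Four unranked primary outcomes, a sample size justified for one test at 0.05, and no rule across them: about 11–19% chance of at least one false positive if each is tested at 0.05

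*Protocol article*

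**What the plan says.** The Outcome measures section gives changes in approach bias as primary, "measured by the assessment versions of the joystick-AAT and the VR-AAT, reductions in nicotine consumption, and abstinence rates". This makes four outcomes: joystick-AAT bias, VR-AAT bias, nicotine consumption and abstinence. None is placed above another.

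The Background says the trial will investigate whether the training is "capable of modifying existing approach biases for smoking cues and/or changing smoking behavior by promoting abstinence or reduction of nicotine consumption". The Discussion repeats the and/or framing. The last sentence of the Background, however, states the expectation for all the outcomes together: lower bias, fewer cigarettes and more abstinence than placebo.

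Trial design calls this a superiority trial and describes its sizing: "We conducted a power analysis for a 2 × 3 mixed design ANOVA". The result was that "a total sample size of 74 is required to achieve 80% power at an alpha level of 0.05", with d = .30 and "an assumed correlation of r = .50 between the repeated measures". Enrolment was set at 100 to allow for attrition. No other significance level appears in the article.

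Data preparation and planned analyses assigns these tests:

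- **Approach biases:** a condition × item content × time mixed ANOVA.
- **Consumption, self-report:** "To evaluate the effects of training on self-reported average daily nicotine consumption, a 2 × 3 mixed ANOVA will be carried out".
- **Consumption, app data:** "Multilevel modeling (MLM) will be used to estimate the growth curve for nicotine consumption as measured with the cigarette-training app", in a sentence that also covers craving.
- **Abstinence:** one chi-square test, with no time point named.

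The same section places a multivariate test ahead of separate ANOVAs for CO, FTND, smoking attitude and motivation to quit. None of these is a primary outcome.

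**The concern.** A superiority trial with several primary outcomes needs to say how they combine into a conclusion. If all must succeed, no adjustment of alpha is needed, but power falls. If any one may succeed, the error rate across the set must be controlled. This article lists four primaries side by side, words the aim as and/or, and justifies the sample size as though there were one test at 0.05. The one multivariate gate it describes protects variables outside the primary set.

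Read as written, the plan would let a single nominally significant result among the four be reported as a positive finding on a primary outcome. The chance of that when the training does nothing is well above the 5% that the sample-size statement suggests.

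**Working it through.** **1. Reproduce the plan's own figure.** The inputs are from Trial design: d = 0.30, so f = d/2 = 0.15; m = 3 time points; two groups; correlation ρ = 0.50; alpha = 0.05. For the condition × time interaction:

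- noncentrality λ = N·m·f²/(1 − ρ), with 2 and 2(N − 2) degrees of freedom
- at N = 74, λ = 74 × 3 × 0.0225 / 0.5 = 9.99, with 2 and 144 degrees of freedom, giving power 80.6%
- at N = 72, power is 79.5%

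The smallest total with equal groups is therefore 74, as stated. The arithmetic is sound, and it applies to one interaction test at 0.05.

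**2. Error rate if each of the four primaries is tested at 0.05.** For k independent tests with no true effect, the chance of at least one false positive is 1 − 0.95^k:

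- k = 4: 1 − 0.8145 = 18.5%
- k = 5 (app growth curve also counted): 1 − 0.7738 = 22.6%
- k = 3 (abstinence left out): 1 − 0.8574 = 14.3%

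**3. Allow for correlation.** The article gives no correlation between outcomes, so these values are assumptions. They come from simulated two-sided normal tests with a common pairwise correlation.

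| Common correlation | Four tests | Five tests |
|---|---|---|
| 0 | 18.5% | 22.6% |
| 0.3 | 17.4% | 20.9% |
| 0.5 | 15.6% | 18.3% |
| 0.7 | 13.1% | 14.9% |
| 0.8 | 11.4% | 12.7% |

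Over this range, four tests give about 11% to 19%.

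**4. Cost of control.** Holm compares the smallest of four p-values with 0.05/4 = 0.0125. The formula in step 1 at that level gives:

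| Analysed | λ | Power at 0.05 | Power at 0.0125 |
|---|---|---|---|
| 74 | 9.99 | 80.6% | 62.6% |
| 100 | 13.5 | 91.4% | 79.6% |

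Reaching 80% at 0.0125 takes 102 analysed participants. These figures apply to a 2 × 3 interaction. They do not cover the chi-square test, or a VR-AAT comparison with only two time points.

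**The case against.** Four points can be made for the plan.

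- **The level per test is inferred.** 0.05 appears only in the power analysis, and multiplicity rules are often kept in an SAP or full protocol, neither of which is shown. This stands as a caution, and the missing rule alone would not be a finding. But the article itself fixes four unranked primaries and a sample size for one test at 0.05. If a stricter level is intended elsewhere, the power statement no longer describes the trial.
- **One success is not stated to be enough.** A reader might infer from the and/or wording that any positive result will be declared efficacy. The article does not say so. The sentence describes what is to be investigated, and the hypothesis that follows joins the outcomes. What stands is that the article settles on neither rule.
- **The growth curve is not called primary.** A reader might count five primary tests and quote an error rate of up to 23%. The article does not establish that. It uses the multilevel model to estimate a curve, alongside craving, which is secondary, and names no condition test for it. Its status is left open, so four tests is the supported count.
- **Abstinence is introduced as something to explore.** That wording sits uneasily with its listing as primary. Leaving it out still gives 14.3% for three independent tests.

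Correlation between outcomes lowers the figure, but even at 0.8 four tests give more than twice 5%.

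**Conclusion.** The point holds in a limited form. The article lists four primary outcomes without ranking them, frames the aim as and/or, and sizes the trial for one test at 0.05 with no stated order or correction across the set. If each is tested at 0.05, the chance of at least one false positive is 18.5% under independence and about 16% to 11% at assumed common correlations of 0.5 to 0.8. This rests on three assumptions: 0.05 per test, one test per outcome, and correlations that the article does not supply. The 22.6% figure applies only if the app growth curve is also read as a primary test and all five tests are independent.

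The sample-size arithmetic is correct, and the data remain fully usable. What needs settling before analysis is how the four results support a claim of efficacy.

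**What to change.** Keep the four primary outcomes, name one test for each, and apply Holm across the four:

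1. Joystick-AAT: the condition × item content × time interaction.
2. VR-AAT: the same interaction, over the time points at which it is actually measured. Procedure places this assessment before the first and after the last training session, whereas Cognitive bias assessment and the planned analyses imply three occasions. These sections must be reconciled first.
3. Self-reported average daily consumption: the condition × time interaction.
4. Abstinence: the chi-square test at the 7-week follow-up.

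Label the app growth curve a supportive analysis of consumption. State that efficacy will be claimed only for outcomes that survive Holm.

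No new data are needed. The cost is power: the smallest p-value must meet 0.0125, where the protocol's own inputs give 62.6% with 74 analysed and 79.6% with 100. Later Holm steps (0.05/3 = 0.0167, 0.025, 0.05) are milder. The power statement should be revised to report this. Trial status records 108 enrolled, against the 102 analysed needed for 80% at the strictest step, so attrition decides whether that power is reached. Trial status also shows recruitment still open and results yet to come, so the rule could be fixed before analysis.
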